**Table 1 T1:**
[figure not shown]
Trial timeline.

#### Randomization

2.5.2

The randomized list will be generated centrally by an independent statistician before the start of the study and will be kept confidential in a secure environment. The sample sizes of each randomized group will be balanced with a 1:1 ratio. Randomization will be stratified in the investigating centers to take into account the potential differences in the characteristics of women consulting these centers. A validated web-based system will be used to implement the random assignment to each group.

After completion of the baseline assessment, the investigator will log onto the study e-CRF and complete the “Randomisation” web page with the eligibility criteria and validate the content. The website will then immediately list the treatment assigned to the trial participant.

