#### Sample size calculation

2.7.2

We assume rates for successful treatment of anorectal *C. trachomatis* infection of 99% for doxycycline and 83% for azithromycin and a loss of follow-up of 10%. Missing values will be replaced by a failure of the treatment in the intention-to-treat primary analysis. Therefore, to compare 89.1% versus 74.7%, with a 2-sided type 1 error rate of 5% and a power of 90% for a Chi-squared test, the sample size is estimated at 149 patients per group (SAS, proc power v9.3).

According to the pilot study, the prevalence of anorectal *C. trachomatis* infection concurrent with urogenital infection was 75% with 95% confidence interval (95% CI) = (65*–*84%) in our population. For our trial, we made the conservative assumption of a prevalence of 65% of anorectal *C. trachomatis* infection concurrent with urogenital infection at inclusion; therefore, we will include 230 women per group and 460 women in total.

With a total of 460 women enrolled, we will be able to estimate the prevalence of concurrent anorectal and urogenital infections with the following precision:

(1)for a prevalence of 65%: 95% CI = (60.5*–*69.3)(2)for a prevalence of 75%: 95% CI = (70.8*–*78.9)

According to the data of the 7 participating centers in 2015, we have a potential number of 1115 eligible women with *C. trachomatis* positive vaginal specimens.

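### Randomization is stratified by centre, but the stated adjustment rule will seldom bring centre into the primary comparison; stratifying the analysis is a minor improvement at almost no cost

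*Protocol article*

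**What the plan says.** All references are to the protocol article; the statistical analysis plan is not shown.

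- **Section 2.5.2, Randomization.** "The sample sizes of each randomized group will be balanced with a 1:1 ratio", and "Randomization will be stratified in the investigating centers to take into account the potential differences in the characteristics of women consulting these centers". Section 2.3 lists the strata: four STI screening centres and three pregnancy termination centres.
- **Section 2.7.2, Sample size calculation.** The trial is sized "to compare 89.1% versus 74.7%, with a 2-sided type 1 error rate of 5% and a power of 90% for a Chi-squared test", and "the sample size is estimated at 149 patients per group". This is the only place where a comparative test is named.
- **Section 2.8, Analysis.** No test or model is named for the primary outcome, and centre does not appear. Comparative analyses are to be adjusted for baseline prognostic factors only where these prove unbalanced between the arms.

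**The concern.** When randomization is stratified on a factor that predicts outcome, the arms are balanced on it by design. The difference in proportions then varies less from trial to trial than the simple binomial formula assumes. An analysis that ignores the strata has standard errors that are somewhat too large, a type I error below the nominal level, and less power than it could have.

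The adjustment rule in section 2.8 works against correcting this. Centre is the one factor that the design deliberately balances, so a rule triggered by observed imbalance is the least likely to pick it up.

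Centre could plausibly predict outcome here. There are two kinds of centre, and women lost to follow-up count as failures. At the planned rates, loss to follow-up supplies 10 of the 10.9 percentage points of doxycycline failure (100 − 89.1) and 10 of the 25.3 points of azithromycin failure (100 − 74.7). Attendance therefore matters, and non-attenders are recalled by each centre's own coordinator (section 2.5.5). None of this shows that outcome does differ by centre.

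**Working it through.** **1. The plan's own figure.** Section 2.7.2 assumes success of "99% for doxycycline and 83% for azithromycin and a loss of follow-up of 10"% and states: "Missing values will be replaced by a failure of the treatment in the intention-to-treat primary analysis". So 0.99 × 0.90 = 0.891 and 0.83 × 0.90 = 0.747, with mean 0.819 and difference 0.144.

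n per group = [1.960 × √(2 × 0.819 × 0.181) + 1.282 × √(0.891 × 0.109 + 0.747 × 0.253)]² / 0.144²

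= [1.960 × 0.5445 + 1.282 × 0.5349]² / 0.020736 ≈ 148.1, rounded up to 149.

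Power at 149 per group is 90.2%. Also 149 / 0.65 = 229.2, hence 230 per group and 460 in total. The stated sample size is reproduced.

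**2. Why the unstratified standard error can be too large.** With centre success rates p_k, the overall variance p̄(1 − p̄) equals the mean of p_k(1 − p_k) plus the between-centre variance of p_k. With balance within centres, only the first part contributes to the sampling error of the difference. The second part is the excess. It is zero if centres do not differ.

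**3. Size with exact balance within centre.** The between-centre spread is not in the documents, so it is an assumption, shown as a range of SDs on the logit scale. Set-up: seven equal centres, 149 per arm, fixed centre effects, marginal rates held at 89.1% and 74.7% (81.9% in both arms under the null), 100,000 runs per setting. CMH is the Cochran-Mantel-Haenszel test stratified by centre. The SE ratio is the unstratified standard error divided by the true sampling SD, at the design rates.

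| Centre SD | Success by centre, doxycycline | Success by centre, azithromycin | SE ratio | Type I error, chi-squared / CMH | Power, chi-squared / CMH |
|---|---|---|---|---|---|
| 0 | 89.1% | 74.7% | 1.00 | 5.1% / 5.1% | 90.8% / 90.8% |
| 0.25 | 84.9–92.6% | 66.7–81.8% | 1.00 | 5.0% / 5.0% | 91.0% / 91.1% |
| 0.5 | 80.1–95.3% | 58.4–87.5% | 1.01 | 4.5% / 4.9% | 91.4% / 91.9% |
| 0.75 | 75.1–97.1% | 50.2–91.8% | 1.04 | 4.1% / 5.0% | 91.7% / 92.7% |
| 1.0 | 70.2–98.3% | 42.6–94.9% | 1.07 | 3.7% / 5.0% | 92.5% / 94.1% |

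Hand check at SD 1.0: under the null the SE ratio is 1.066, so the effective critical value is 1.960 × 1.066 = 2.089. The two-sided normal tail beyond that is 3.7%, as simulated.

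**4. Size with the planned rates held and a second simulation of centre effects.** Power is 90.9% (chi-squared) against 91.4% (CMH) at SD 0.5, a gap of 0.5 points, and 90.8% against 92.4% at SD 1.0, a gap of 1.6 points. Chi-squared type I error is 4.7% and 3.8%. The gaps match step 3.

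**5. The analysed subset.** Strata balance all women randomized, but the primary population is only those with a positive anorectal swab at baseline. Taking 230 randomized per arm, each positive with probability 0.65, balance within centre is looser. Chi-squared type I error is then 4.8% at SD 0.5 and 4.4% at SD 1.0, so the conservatism is smaller than with exact balance.

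**The case against.** The strongest objection is that the article never commits to an unstratified analysis. The chi-squared test is named to size the trial, section 2.8 names no primary test, and an article may leave the model to an analysis plan that is not shown. That stands as far as the test is concerned: a reader might infer that the primary analysis is fixed as unstratified, and the text does not say so. It does not dispose of the point, because section 2.8 does fix the rule for adjustment, and that rule is poorly suited to a stratification factor.

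A second objection is that standard errors are too large only if outcome differs by centre. This also stands. Section 2.5.2 speaks of possible differences in the women. Section 2.5.6 says that each laboratory runs its routine NAAT, not that the assays differ. No centre-specific cure or loss rates are given.

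A third is that the effect is small, and this stands too. A reader might infer that ignoring centre takes power below the planned 90%. That result appears only if centre effects are added on the logit scale without recalibration. At SD 1.0 the marginal rates then drift to 85.6% and 71.1%, and power is 87.3% (chi-squared) against 89.6% (CMH). Most of that shortfall comes from the changed rates and falls on both tests. With the planned rates held, both stay above 90%.

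**Conclusion.** The point holds as a minor one. The design stratifies by centre, the only test named is unstratified, and the adjustment rule will seldom bring centre in. If outcome varies by centre, the cost is a slightly conservative test and a loss of about 0.5 points of power at a centre SD of 0.5, or about 1.5 points at SD 1.0. The latter is an extreme spread, with azithromycin success ranging from about 43% to 95% across centres. If centres do not differ, nothing is lost.

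The documents do not support calling this a threat to validity. Type I error is not inflated, and the sample size of 149 per group and the 90% power both stand. The magnitudes rest on an assumed logit-scale spread and seven centres of equal or similar size; the direction does not depend on those choices.

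**What to change.** In section 2.8, state that the primary comparison is stratified by centre whatever the observed baseline balance: a Cochran-Mantel-Haenszel test, with the Mantel-Haenszel risk difference and its 95% CI as the effect estimate. Very small centres are pooled within centre type (STI screening or pregnancy termination) by a rule set in advance. Keep the unstratified chi-squared test as a check.

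The cost is one sentence there and a matching one in the statistical analysis plan. If that plan already stratifies by centre, only the protocol text needs aligning. The sample size does not change.

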#### Intervention

2.5.3

Participants will be randomly allocated to one of the following treatment groups:

(1)Azithromycin: women in the azithromycin group will take four tablets of 250 mg as a single dose.(2)Doxycycline: Treatment with doxycycline will consist of administration of 1 tablet of 100 mg of doxycycline twice daily in the morning and evening for 7 days. Doxycycline tablets will be taken at mealtimes with a glass of water (minimum 100 mL) and at least 1 hour before bedtime. Women will be advised to take antacids, iron supplements, zinc supplements, and didanosine at least 2 hours after taking the doxycycline. Women will be advised to minimize sun exposure or use sunscreen to reduce the risk of photosensitivity.

Antibiotics will be dispensed in their usual packaging with a clinical trial label.

#### Follow-up at 6 weeks

2.5.4

All women will be asked to attend the participating center 6 weeks after treatment initiation.

During this visit, the research nurse will look at the *C. trachomatis* detection result of the anorectal swab performed at baseline. If no *C. trachomatis* was detected, the study will end. If the detection of *C. trachomatis* is positive, patient will be asked to provide new self-collected vaginal and anorectal swabs for *C. trachomatis* detection (Fig. 1).

The research nurse will complete the e-CRF questionnaire about drug adherence. Participants will return the treatment box for a pill count as a proxy measure of drug adherence. Women will be asked whether they have experienced any diarrhea or vomiting that could affect the levels of antibiotic absorption, or any adverse events. Clinical data during the last 6 weeks (vaginal discharge, pelvic pain, abnormal bleeding, pain during sexual intercourse, anal discharge, anal itching, and tenesmus) and information about whether they have taken any other antibiotics will be collected.

Participants will complete a questionnaire about their sexual behavior during the last 6 weeks [sexual intercourse with a regular or occasional partner, nature of the intercourse (genital and/or anal and/or oral), and use of condoms] and their partner's treatment (Table 1).

At this stage, the study will end for all women with *C. trachomatis* negative vaginal and anorectal swabs and for those with a *C. trachomatis* positive vaginal swab (whatever the result of the anorectal swab) (Fig. 1). Women with a *C. trachomatis* positive vaginal swab will be informed by the practitioner at each center, who will provide treatment and information on the need for their partner(s) to be treated (usual recommendations).

Women with a *C. trachomatis* negative vaginal swab and a *C. trachomatis* positive anorectal swab will be asked to attend the participating center 4 months after treatment initiation (Fig. 1).

#### Follow-up at four months

2.5.5

Participants will provide self-collected vaginal and anorectal swabs for *C. trachomatis* detection.

The research nurse will collect information on the e-CRF about other antibiotics taken and clinical data since the last visit (vaginal discharge, pelvic pain, abnormal bleeding, pain during sexual intercourse, anal discharge, anal itching, and tenesmus) (Table 1).

Participants will complete a questionnaire about their sexual behavior since the last follow-up visit [sexual intercourse with a regular or occasional partner, nature of the intercourse (genital and/or anal and/or oral), and use of condoms] and partner's treatment.

Data collected regarding participants will be anonymized.

If the participant does not attend the follow-up visit scheduled, the study site coordinator of each center will contact her by phone to schedule a new appointment within the 2 following weeks. To compensate participants for the time dedicated to the study, financial compensation will be given at the follow-up visits.

In the case where participants do not complete follow-up, attempts will be made to obtain information on the reasons for dropout. The last contact will be recorded.

#### Specimen processing

2.5.6

For each specimen, the detection of *C. trachomatis* will be carried with a routine NAAT at each laboratory of the corresponding participating center. All *C. trachomatis* positive specimens will be sent to the National Reference Centre for bacterial STI for genotyping (Table 1).

#### Genotype determination

2.5.7

DNA will be extracted using the automated MagNA Pure 96 isolation and purification systems (Roche Diagnostics, Meylan, France). A method based on sequencing of the *omp1* gene will be performed to determine the strain genovar on sequential samples.^[23]^ If the genovars are the same, a molecular method based on multilocus variable number tandem repeat analysis (MLVA),^[24]^ which is able to discriminate strains belonging to the same genovar, will be performed. Both methods can be directly applied to the clinical specimens without a cell-culturing step.

### Outcomes

2.6

#### Primary outcome

2.6.1

The primary outcome is the microbial cure rate defined as a C. *trachomatis* negative NAAT result in anorectal specimens 6 weeks after treatment initiation (with azithromycin and doxycycline) among women with a C. *trachomatis* positive vaginal and anorectal NAAT result at the baseline.

#### Secondary outcomes

2.6.2

We will estimate the prevalence of anorectal *C. trachomatis* infection concurrent with urogenital infection. The prevalence will be defined at the baseline by the number of women with an anorectal *C. trachomatis* infection divided by the total number of women included in the study.

For each participant, we will further determine the *C. trachomatis* genotype profile in order to identify whether the same *C. trachomatis* genotype profile is found in the vaginal-positive and anorectal-positive specimens.

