#### Recruitment

2.5.1

Women with a *C. trachomatis* positive vaginal swab at the baseline will be approached by a research nurse and invited to take part in the trial (Fig. 1). The nurse will explain the trial and investigator will assess eligibility and obtain consent. Eligible women will be enrolled. Participants will provide a self-collected anorectal swab. Previous studies have found high feasibility and acceptability of self-collected anorectal testing in women who do not have an indication.^[10,11]^

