**Figure 1 F1:**
[figure not shown]
Design of the Chlazidoxy study.

All women with urogenital *C. trachomatis* infection will be included without waiting for the NAAT result of the anorectal specimen because treatment cannot be delayed. However, the study population will consist of only women with both *C. trachomatis* positive vaginal and anorectal swabs.

Information on the need for partner(s) to be treated will be provided. Sexual abstinence or protected intercourse with the partner(s) up to 7 days after the single dose of azithromycin or after 7 days of doxycycline will be recommended (usual recommendations).

The research nurse will complete an electronic Case Report Form (e-CRF) at the time of recruitment of the demographic characteristics (birth date, country of birth, marital status, education level, professional status), and biological (previous *C. trachomatis* infection, HIV-serology, *Neisseria gonorrhoeae* infection, hepatitis B virus, and syphilis serology) and clinical data (vaginal discharge, pelvic pain, abnormal bleeding, pain during sexual intercourse, anal discharge, anal itching, tenesmus). Participants will complete a questionnaire about their sexual behavior [regular sexual partner(s), occasional sexual partner(s) in the last 12 months, use of condoms, anal and oral intercourse] (Table 1).

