#### Pilot study

2.7.1

We conducted a pilot study to evaluate the percentage of women with concurrent urogenital and anorectal *C. trachomatis* infections, in the same population and at the same centers as the trial, to measure the size of the population to be tested. A total of 100 women with a self-collected vaginal swab positive for *C. trachomatis* using NAAT were included and provided self-collected anorectal swabs for *C. trachomatis* detection. Overall, 77.1% (74/96) were positive for anorectal *C. trachomatis*. These results highlight the feasibility of our study.

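### Baseline anorectal prevalence is divided by all women included, so any woman without a valid anorectal result counts as uninfected and the estimate is biased downward

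*Protocol article*

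**What the plan says.** Section 2.6.2 (Secondary outcomes) defines baseline prevalence as the count of women with anorectal infection "divided by the total number of women included in the study". Section 2.5.1 (Recruitment) settles who is included: "All women with urogenital *C. trachomatis* infection will be included without waiting for the NAAT result of the anorectal specimen". The same section states "Participants will provide a self-collected anorectal swab", but the inclusion criteria in section 2.4.1 require only a positive vaginal NAAT, not an anorectal result.

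Section 2.7.2 (Sample size calculation) uses the same denominator for the promised precision: "With a total of 460 women enrolled, we will be able to estimate the prevalence of concurrent anorectal and urogenital infections". The intervals given there are 60.5 to 69.3% at a prevalence of 65% and 70.8 to 78.9% at 75%.

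Section 2.7.1 (Pilot study) reports "A total of 100 women with a self-collected vaginal swab positive for *C. trachomatis* using NAAT were included and provided self-collected anorectal swabs", and then "Overall, 77.1% (74/96) were positive for anorectal" infection. Four of the 100 women are not in that denominator, and no reason is given.

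Section 2.8 (Analysis) applies its missing-equals-failure rule to the primary endpoints. For all variables it promises a count of missing data and, as far as possible, the reasons. It gives no rule for missing anorectal results in the prevalence outcome.

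**The concern.** The numerator can contain only women with a positive anorectal result, whereas the denominator contains every woman enrolled. A woman whose swab is not provided, is lost or gives an invalid test is therefore treated exactly like a woman with a negative test. The error has one direction: each missing result can only lower the estimate.

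This is a stated rule, not a detail left for later. It also differs from what the pilot did in the same population and centers, so the trial and pilot prevalences would not be computed alike. Prevalence is the first of the secondary outcomes in section 2.6.2 and has its own precision statement. A bias of a few points matters against an interval meant to reach only about 4 points either side.

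**Working it through.** **Inputs from the article.** Pilot: 74 positives, denominator 96, 100 women included (2.7.1). Trial: 460 enrolled, with prevalence scenarios of 65% and 75% (2.7.2). Confidence intervals: exact binomial (2.8).

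**Input assumed.** The share *m* of women without a valid baseline anorectal result is not given for the trial. I take 4% as the central value, because 4 of 100 pilot women are outside the denominator, and show 0 to 10%. Missingness is assumed independent of infection status.

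**Step 1: reproduce the plan's figures.** 74/96 = 77.1%, as stated. The exact 95% CI for 345/460 = 75% is 70.8 to 78.9%, as stated. For 299/460 = 65% it is 60.4 to 69.4%, against 60.5 to 69.3% stated, a negligible difference. The half-width at 75% is (78.9 − 70.8)/2 = 4.05 points.

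**Step 2: apply the trial's rule to the pilot.**
- Denominator 96: 74/96 = 77.1% (exact 95% CI 67.4 to 85.0%).
- All women included: 74/100 = 74.0% (64.3 to 82.3%).
- Difference: 77.1 − 74.0 = 3.1 points.

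**Step 3: project to the trial.** With true prevalence *p*, the rule estimates *p*(1 − *m*), so the bias is −*pm*. Coverage is the probability that the exact 95% CI, computed from a binomial count with n = 460 and probability *p*(1 − *m*), contains *p*. For *p* = 75%:

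| *m* | Expected estimate | Bias (points) | Coverage of 75% |
|---|---|---|---|
| 0% | 75.0% | 0 | 95% |
| 1% | 74.25% | −0.75 | 94% |
| 2% | 73.5% | −1.5 | 89% |
| 4% | 72.0% | −3.0 | 69% |
| 5% | 71.25% | −3.75 | 55% |
| 10% | 67.5% | −7.5 | 6% |

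At *m* = 4% and a true 65%, the expected estimate is 0.65 × 0.96 = 62.4% and coverage is about 79%.

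**Step 4: compare denominators at *m* = 4%, true 75%.** Women with a result: 460 × 0.96 ≈ 442. Positives: 460 × 0.96 × 0.75 ≈ 331. Women without a result: 460 − 442 = 18.
- All included, the 18 counted as negative: 331/460 = 72.0% (67.6 to 76.0%).
- Valid results only: 331/442 = 74.9% (70.6 to 78.9%).
- All included, the 18 counted as positive: (331 + 18)/460 = 349/460 = 75.9%.

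The valid-result interval is (78.9 − 70.6)/2 = 4.15 points either side, against 4.05 with all 460 results available.

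**The case against.** The strongest reply is that this is a one-sentence definition in a condensed article, for a descriptive outcome. Every participant is expected to give a swab, randomization follows completion of the baseline assessment, and section 2.8 already promises counts of missing data. With few or no missing results the rule does no harm. The dependence on an unknown missing share stands, and the size must be stated conditionally. It does not remove the point: the article fixes a denominator, and counting missing data does not change that denominator.

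Four stronger readings are tempting, and the article does not support them.

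- *The pilot counted valid results only.* This is plausible, but section 2.7.1 says that all 100 women provided swabs and does not explain the 96. Another reason for exclusion is possible.
- *The interval would largely miss the true value.* At 4% missing, the expected interval of 67.6 to 76.0% still contains 75%, and coverage is about 69%. That is well below 95%, but it is not a general miss.
- *The result would not be comparable with the 65% planning value.* Section 2.7.2 uses 65% as the yield of doubly positive women per woman enrolled (149/0.65 = 229.2, stated as 230 per group). Positives over all included is that same quantity.
- *A change in treatment recommendations rests on this estimate.* The Discussion makes any revision depend on doxycycline proving more effective, which is the primary comparison. Prevalence is background to that argument.

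**Conclusion.** The point holds. As written, the prevalence definition treats women without a valid anorectal result as uninfected and can only understate prevalence. Under the assumption of 4% missing, independent of infection status, the understatement is about 3 points at a true 75%. That is about three quarters of the promised half-width (3.0/4.05 = 0.74). The effect shrinks to 0.75 points at 1% missing and vanishes if every woman has a result. If missingness were related to infection status, the distance from the truth would differ but the direction would not. The issue is confined to a descriptive secondary outcome; the primary comparison, its power and the enrolment of 460 are untouched. It should be corrected because the rule is explicit, it differs from the pilot's calculation, and the change is cheap.

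**What to change.** Replace the definition in section 2.6.2 with: women with a positive baseline anorectal NAAT divided by women with a valid baseline anorectal NAAT, with an exact 95% CI. Report the number of women without a valid result. Give two bounds on all women included, one counting those women as negative (the present definition) and one counting them as positive. State in section 2.7.1 why the pilot denominator is 96, so that the two prevalences can be compared on the same basis.

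The cost is one or two sentences and a very slightly wider interval: about 442 instead of 460 women at 4% missing. The valid-result estimate still assumes that women without a result resemble those with one, and the two bounds show how much depends on that. Fixing the denominator now also avoids choosing it once the results are known.
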